### Anaesthesia regimen

No pre-induction drugs will be administered to avoid latent interference effects with FVEPs. Baseline parameters will be monitored perioperatively, including blood pressure, electrocardiogram (ECG), pulse oxygen saturation, bispectral index (BIS), and body temperature. Anesthesia induction and maintenance of propofol will be conducted with a target-controlled infusion (TCI) device (Marsh model, Master TCI-Diprifusor, Fresenius, Brezins, France). After 5 min of preoxygenation, general anesthesia induction will be performed by sequence TCI propofol 5 μg/ml, bolus of remifentanil 1–2 μg/kg, and rocuronium 0.6 mg/kg intravenously to complete tracheal intubation. Respiratory parameters will be adjusted to a tidal volume of 8 ml/kg and a respiratory rate of 10–12 breaths/min; PaCO_2_ will be maintained at 35–45 mmHg. After induction of anesthesia, all patients will be maintained with TIVA (propofol 3–4 μg/ml plasma concentration and remifentanil 0.05–0.2 μg/kg/min) for 30 min to obtain baseline FVEP values. Next, for the patients in the HD group, we will administer desflurane (0.7–1.0 MAC of end-tidal concentration) and remifentanil (0.05–0.2 μg/kg/min) for maintenance, while desflurane (0.5 MAC) will be combined with propofol (1.5–2.5 μg/mL) and remifentanil (0.05–0.2 μg/kg/min) in the LD group. The plasma concentration of propofol will be adjusted in the LD group, and the MAC of desflurane will be titrated between 0.7 and 1.0 to maintain the BIS (BIS Vista monitor, Aspect Medical Systems, Natick, MA) between 40 and 50, primarily focusing and avoiding burst suppression. The mean arterial pressure (MAP) and heart rate (HR) will be maintained at ± 10% compared with baseline. The anesthesiologist will give vasoactive drugs such as urapidil, dopamine, esmolol, and atropine if the blood pressure and heart rate fluctuate >  ± 10%. Intraoperative body temperature will be maintained between 36 and 37°C.

### Intervention

An ophthalmologist will examine all patients to ensure normal visual function one day before the surgery. The patients will also undergo intraoperative neurophysiological monitoring using electrodes placed subcutaneously or in a corkscrew, including FVEPs and electroretinography (ERG) monitoring (to ascertain efficient delivery of retinal light stimulation).

The corkscrew electrodes for FVEPs will be located in the occipital zero (OZ) (4 cm above the occipital trochanter), O1 (4 cm left lateral to the OZ), O2 (4 cm right lateral to the OZ), frontal zero (FZ) (midfrontal area, 10–12 cm above the nose), and 2 ground electrodes. Electrodes for ERG will be placed 2 cm from the lateral canthus of the patient’s eyes (Fig. 3). FVEP stimulation, data recording, and storage will be performed using the Medtronic NimEclipse neuromonitoring system, which provides goggles with 6 embedded light-emitting diode (LED) bulbs. The specific parameters will be as follows: white light source high-intensity LED, 1.1 Hz stimulation frequency, 5000 to 10,000 lx laser emission, smoothing bandpass 20 to 100 Hz, and 1 to 100 Hz filter bandpass [21–23]. Each pulse stimulation will last 10 ms. The same experienced neuroelectrophysiologist will monitor intraoperative FVEPs for all procedures. We named the vertical distance between N75 and P100 the N75-P100 amplitude and the vertical distance between P100 and N145 the P100-N145 amplitude and defined P100 as the latency of FVEPs in our study. We will measure the baseline amplitude and latency of FVEPs 30 min after anesthesia induction under TIVA in both groups, which will be marked as N75-P100 (TIVA), P100-N145 (TIVA), and P100 (TIVA). Then, anesthesia maintenance with the HD group or LD group will be implemented according to the randomization results. We will measure the amplitude and latency of FVEPs 60 min after anesthesia induction in LD or HD group, which will be accordingly marked as N75-P100 (LD), P100-N145 (LD), and P100 (LD) vs N75-P100 (HD), P100-N145 (HD), and P100 (HD). At each chosen time point, we will measure the N75-P100 amplitude, P100-N145 amplitude, and P100 latency 3 times and record the average of the measurements.

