**Fig. 2 Fig2:**
[figure not shown]
Flow diagram: the schedule of enrollment, interventions, and assessments. LD, low inhaled concentration of desflurane combined with propofol-remifentanil-balanced anesthesia; HD, high inhaled concentration of desflurane combined with remifentanil anesthesia

Randomization will occur on the date of spine surgery. Block randomization will be conducted to allocate patients to the LD group or HD group at a 1:1 ratio. The randomized digital table will be generated by an independent researcher using SPSS 25 and will be placed in a closed, opaque envelope. A designated person not involved in anesthesia management or follow-up will perform the assignment randomization sequence to ensure blinding. After the patient enters the operating room, the attending anaesthesiologist will open the sealed envelope to obtain the assignment information.

The neuroelectrophysiologists (primary outcome assessors), neurosurgeons, follow-up assessors, and biostatisticians will be blinded to the grouping; however, the anaesthesiologists will be aware of the specific assignments, as the interventions in this trial require different anesthesia protocols. A designated experienced neuroelectrophysiologist will monitor intraoperative FVEPs for all patients.

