### Study endpoints

FVEP stimulation, data recording, and storage will all be performed using the Medtronic NimEclipse neuromonitoring system. The same experienced neuroelectrophysiologist will monitor intraoperative FVEPs for all procedures.

The primary endpoint of this study is the N75-P100 amplitude at 60 min after the induction of anesthesia, which is defined as the mean N75-P100 amplitude on O1, O2, and Oz leads in both eyes.

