The secondary endpoints are as follows:N75-P100 amplitude decline rate compared to baseline measured under TIVA, calculated by the formula $$\frac{\left[N75-P100\left(TIVA\right)-N75-P100\left(HD\right)\right]}{\left[N75-P100\left(TIVA\right)\right]}\times100\%$$ or $$\frac{\left[N75-P100\left(TIVA\right)-N75-P100\left(LD\right)\right]}{\left[N75-P100\left(TIVA\right)\right]}\times100\%$$. N75-P100 (TIVA) will be measured 30 min after anesthesia induction under TIVA in both groups. N75-P100 (HD) or N75-P100 (LD) will be measured 60 min after anesthesia induction in HD or LD group.P100-N145 amplitude decline rate compared to baseline measured under TIVA, calculated by the formula $$\frac{\left[P100-N145\left(TIVA\right)-P100-N145\left(HD\right)\right]}{\left[P100-N145\left(TIVA\right)\right]}\times100\%$$ or $$\frac{\left[P100-N145\left(TIVA\right)-P100-N145\left(LD\right)\right]}{\left[P100-N145\left(TIVA\right)\right]}\times100\%$$. P100-N145 (TIVA) will be measured 30 min after anesthesia induction under TIVA in both groups. P100-N145 (HD) or P100-N145 (LD) will be measured 60 min after anesthesia induction in HD or LD group.Rate of prolongation of P100 latency compared to TIVA baseline measurements, calculated by the formula $$\frac{\left[P100\left(HD\right)-P100\left(TIVA\right)\right]}{\left[P100\left(TIVA\right)\right]}\times100\%$$ or $$\frac{\left[P100\left(LD\right)-P100\left(TIVA\right)\right]}{\left[P100\left(TIVA\right)\right]}\times100\%$$. P100 (TIVA) will be measured 30 min after anesthesia induction under TIVA in both groups. P100 (HD) or P100 (LD) will be measured 60 min after anesthesia induction in HD or LD group.The success rate of FVEP monitoring is defined as the ratio of the number of eyes with a satisfactory waveform to the number of all monitored eyes.FVEP stacking satisfaction will be assessed by electrophysiologists. A satisfactory waveform that could be evoked no more than three times will be considered satisfactory.Intraoperative anesthetic and vasoactive drug dosage, including anesthetics (i.e., sufentanil, remifentanil, propofol, rocuronium) and vasoactive agents (i.e., atropine, ephedrine, noradrenaline, phenylephrine, urapidil)Recovery quality:Respiratory recovery time is defined as the time from the cessation of anesthesia to the patient’s spontaneous breathing.Eye-opening time is the time from anesthesia cessation to when the patient can be called to open their eyes.Extubation time is defined as the time from the cessation of anesthesia to the removal of the patient’s tracheal catheter.Post-extubation agitation score. Ratings will be performed immediately after awakening and 15, 30, and 60 min after awakening: 1 point—restful sleep; 2 points—awake and calm; 3 points—irritability or irritability or crying; 4 points—difficulty to comfort or uncontrollable crying; 5 points—unable to be quiet or confused or delirium.Post-extubation sedation score. Ramsay sedation scale will be administered to the patients immediately after awakening and at 15, 30, and 60 min after awakening: 1 point—awake but anxious and restless; 2 points—cooperation, orientation, quiet; 3 points—drowsiness and response to commands; 4 points—drowsiness, rapid response to tapping eyebrow or loud auditory stimuli; 5 points—lethargy, slow response to tapping eyebrow or loud auditory stimuli; 6 points—drowsiness, no response at all. Scores 2–4 indicate satisfactory sedation and 5 to 6 excessive sedation.

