### Data management

Dedicated persons will manage all the data. We intend to use the dual measure evaluation, dual data entry, and statistical analysis by double trained assessors to ensure the reliability and accuracy of the results. They will photograph all paper versions of the original materials and store them in an encrypted database. All electronic data will be stored in the electronic medical system of Beijing Tiantan Hospital. The electronic data of FVEPs will be saved in the Medtronic NimEclipse neuromonitoring system by the same neuroelectrophysiologist.

Patients’ personal information will be appropriately hidden, and only research-related data will be retained for statistical analysis. Paper materials, including the study protocol, case report form, and informed consent form, will be placed in a dedicated locked cabinet.

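### Assessor blinding is claimed for the primary FVEP amplitude, but the described conduct does not support it: the assessor works in theatre, the regimens differ visibly, and the 60-minute values carry arm names

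*Protocol article*

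**What the plan says.** **Blinding.** Under Randomization and blinding: "The neuroelectrophysiologists (primary outcome assessors), neurosurgeons, follow-up assessors, and biostatisticians will be blinded to the grouping". The stated exception is that "the anaesthesiologists will be aware of the specific assignments, as the interventions in this trial require different anesthesia protocols". The abstract and the design section describe the trial as open-label with patient and assessor blinded.

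**Who acquires the signal.** Under Study endpoints, and in near-identical terms elsewhere: "The same experienced neuroelectrophysiologist will monitor intraoperative FVEPs for all procedures". The Discussion gives stimulation, recording and storage to that same person, and Data management has that person save the files.

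**How values are named.** Under Intervention, the baseline values come first: "which will be marked as N75-P100 (TIVA), P100-N145 (TIVA), and P100 (TIVA"). The 60-minute values follow: "in LD or HD group, which will be accordingly marked as N75-P100 (LD), P100-N145 (LD), and P100 (LD) vs N75-P100 (HD"). The same symbols return in the secondary endpoint formulas, with the explanation that "N75-P100 (HD) or N75-P100 (LD) will be measured 60 min after anesthesia induction in HD or LD group".

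**How values are measured.** "At each chosen time point, we will measure the N75-P100 amplitude, P100-N145 amplitude, and P100 latency 3 times and record the average of the measurements". Data management adds: "We intend to use the dual measure evaluation, dual data entry, and statistical analysis by double trained assessors".

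**What differs between arms.** Under Anaesthesia regimen, both arms share a TIVA baseline at 30 minutes. After that the LD arm keeps a propofol infusion alongside desflurane at 0.5 MAC, and the HD arm has desflurane at 0.7–1.0 MAC with remifentanil and no propofol.

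**The concern.** The primary endpoint is a distance between peaks identified on a waveform of a few microvolts, so it depends to some degree on the reader. Related judgements carry weight too. Electrophysiologists decide whether a waveform is satisfactory, and the Statistical analysis section excludes patients without available FVEP data, so a view on whether a recording is usable can affect who is analysed. The Discussion states in advance that LD is expected to be superior.

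A reader who knows the arm could, without intending it, move the primary amplitude, the decline rates, the success rate and stacking satisfaction in the expected direction. If the blind is not secure, the trial loses its main protection against this on the endpoint that decides its conclusion.

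**Working it through.** The plan gives no figure on this point to reproduce. The main check sets the statements against each other.

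1. *Claim:* the primary outcome assessors do not know the arm, and among the staff the section lists only the anaesthesiologists do (Randomization and blinding).
2. *Presence:* one of these neuroelectrophysiologists monitors every case intraoperatively (Intervention, Study endpoints, Discussion).
3. *Visible cue:* by the 60-minute reading one arm has a propofol infusion and the other does not, and the desflurane level differs (Anaesthesia regimen). The article describes nothing that would hide this from the person recording.
4. *Label:* the 60-minute values are named by arm. Anyone who files a value under such a name knows the arm at that moment. The sentence names no actor beyond the study team, and it does not say when the label is attached.
5. *Reading:* three measurements are averaged and two assessors are planned, but the article does not say whether they work live or from stored traces, or whether either is masked.

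Statement 1 is compatible with 2 to 5 only if some unstated safeguard lies between acquisition and scoring.

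**Scale, under assumed reading shifts.** Inputs from Sample size calculation: pilot means 3.43 (LD) and 2.37 µV (HD), SDs 0.78 and 0.80, margin 20% of the HD amplitude, 63 evaluable patients, one-sided alpha 0.025.

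- Margin: 0.20 × 2.37 = 0.474 µV.
- Pilot difference: 3.43 − 2.37 = 1.06 µV, which exceeds the margin by 0.586 µV.
- If readings shift by a fraction *s* upward in LD and downward in HD, the difference moves by *s* × (3.43 + 2.37) = 5.80 *s*:

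| Assumed *s* per arm | Shift in difference (µV) | Share of margin |
|---|---|---|
| 2.5% | 0.145 | 31% |
| 5% | 0.290 | 61% |
| 10% | 0.580 | 122% |

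- Effect on the error rate if the true difference equals the margin exactly, by normal approximation. Pooled SD = √[(0.78² + 0.80²)/2] = 0.790. With 31.5 per arm, SE = 0.790 × √(2/31.5) = 0.199 µV. The chance of declaring superiority is 1 − Φ(1.96 − *b*/SE). For a bias *b* of 0.1, 0.2 or 0.3 µV this is 0.072, 0.170 or 0.325, against a nominal 0.025.

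The documents give no basis for any particular *s* or *b*. These figures show sensitivity, not observed bias.

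**Workload of the remedy.** 70 patients × 2 time points = 140 recordings. With 3 leads and 2 eyes this is 140 × 6 = 840 traces per reader.

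**The case against.** A reader might infer that the supposedly blinded assessor scores the amplitude live and files it under the arm name, so that the blinding claim is false. The text does not go that far.

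- The labelling sentence has the study team as its subject and sits among definitions. Baseline values are named by regimen in the same way, and all these symbols become terms in the formulas. Notation is a natural reading, and a label can be attached at analysis.
- Monitoring is said to be intraoperative, but scoring is not. Traces are stored and duplicate measurement is planned, so later reading is possible.
- Assessors are named in the plural. One person monitors, but the article does not say that this person alone scores.
- The Remedy section gives neurophysiologists and anaesthesiologists separate checks when a recording fails. It describes no shared review of drug settings.
- Knowing the time point does not reveal the arm, because both arms follow the same schedule.
- The assumed shifts are unanchored, and even the 10% case (0.580 µV) stays just below the 0.586 µV by which the pilot difference exceeds the margin.
- A journal article may leave the mechanics of masking to the full protocol, which is not shown.

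All of this stands, and it rules out calling the blind broken. It does not remove the tension. The notation reading leaves the assessor in theatre, stored traces help only if they are read masked, and the point rests on how the stated elements fit together, not on a missing detail alone.

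**Conclusion.** The point holds in limited form. Assessor blinding is asserted for the primary endpoint, but the conduct that the article describes does not support it: intraoperative acquisition by a named assessor, regimens that visibly differ by the 60-minute reading, and arm-coded value names that may be only notation. Loss of blinding is a credible risk and is not shown to have occurred.

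The size of any reading bias is unknown. The scale figures assume a systematic shift that favours LD, the pilot means and SDs, and a margin fixed at 0.474 µV. On those assumptions a bias of 0.1 to 0.3 µV would matter for a true difference near the margin. It would matter less if the true difference is as large as in the pilot.

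**What to change.** Take the primary amplitude and the other FVEP endpoint readings from the stored NimEclipse traces. Export them under codes that hide arm and patient, and preferably time point, and present them in random order. Have the two assessors already planned for duplicate measurement mark them independently, and settle differences before unblinding. Use neutral labels (T30 and T60) in the records, attach the arm only at analysis, and keep the intraoperative reading for clinical use. State in the protocol who reads, from what material, and when the arm is linked. If masked reading of this kind is already the practice, a clarifying sentence and the relabelling are enough.

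The cost is the coded export and the offline marking of about 140 patient-time-point recordings, about 840 traces per reader, and more if each is measured three times. No extra patients or procedures are needed, and recordings already stored can be read in the same way.

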**Fig. 3 Fig3:**
[figure not shown]
Schematic diagram of electrode position for flash visual evoked potential monitoring. OZ, 4 cm above the occipital trochanter; O1, 4 cm left lateral to the OZ; O2, 4 cm right lateral to the OZ; FZ, midfrontal area, 10–12 cm above the nose. ERG, electroretinography

### Remedy

If the FVEPs fail to record, neurophysiologists will check the stimulating apparatus and conditions, such as the stimulus intensity of light, intervals, and waves of ERG, to ensure light conduction and ascertain efficient delivery of retinal light stimulation [17]. The anaesthesiologists will check physiological parameters such as blood pressure, body temperature, and positioning. If an ideal FVEP waveform cannot be obtained after excluding all the above reasons, the surgeon will decide whether to continue the operation. Finally, if the FVEPs fail to record or the surgery is suspended, the patients will remain in the study, but the event will be recorded on the case report form.

### Study endpoints

FVEP stimulation, data recording, and storage will all be performed using the Medtronic NimEclipse neuromonitoring system. The same experienced neuroelectrophysiologist will monitor intraoperative FVEPs for all procedures.

The primary endpoint of this study is the N75-P100 amplitude at 60 min after the induction of anesthesia, which is defined as the mean N75-P100 amplitude on O1, O2, and Oz leads in both eyes.

The secondary endpoints are as follows:N75-P100 amplitude decline rate compared to baseline measured under TIVA, calculated by the formula $$\frac{\left[N75-P100\left(TIVA\right)-N75-P100\left(HD\right)\right]}{\left[N75-P100\left(TIVA\right)\right]}\times100\%$$ or $$\frac{\left[N75-P100\left(TIVA\right)-N75-P100\left(LD\right)\right]}{\left[N75-P100\left(TIVA\right)\right]}\times100\%$$. N75-P100 (TIVA) will be measured 30 min after anesthesia induction under TIVA in both groups. N75-P100 (HD) or N75-P100 (LD) will be measured 60 min after anesthesia induction in HD or LD group.P100-N145 amplitude decline rate compared to baseline measured under TIVA, calculated by the formula $$\frac{\left[P100-N145\left(TIVA\right)-P100-N145\left(HD\right)\right]}{\left[P100-N145\left(TIVA\right)\right]}\times100\%$$ or $$\frac{\left[P100-N145\left(TIVA\right)-P100-N145\left(LD\right)\right]}{\left[P100-N145\left(TIVA\right)\right]}\times100\%$$. P100-N145 (TIVA) will be measured 30 min after anesthesia induction under TIVA in both groups. P100-N145 (HD) or P100-N145 (LD) will be measured 60 min after anesthesia induction in HD or LD group.Rate of prolongation of P100 latency compared to TIVA baseline measurements, calculated by the formula $$\frac{\left[P100\left(HD\right)-P100\left(TIVA\right)\right]}{\left[P100\left(TIVA\right)\right]}\times100\%$$ or $$\frac{\left[P100\left(LD\right)-P100\left(TIVA\right)\right]}{\left[P100\left(TIVA\right)\right]}\times100\%$$. P100 (TIVA) will be measured 30 min after anesthesia induction under TIVA in both groups. P100 (HD) or P100 (LD) will be measured 60 min after anesthesia induction in HD or LD group.The success rate of FVEP monitoring is defined as the ratio of the number of eyes with a satisfactory waveform to the number of all monitored eyes.FVEP stacking satisfaction will be assessed by electrophysiologists. A satisfactory waveform that could be evoked no more than three times will be considered satisfactory.Intraoperative anesthetic and vasoactive drug dosage, including anesthetics (i.e., sufentanil, remifentanil, propofol, rocuronium) and vasoactive agents (i.e., atropine, ephedrine, noradrenaline, phenylephrine, urapidil)Recovery quality:Respiratory recovery time is defined as the time from the cessation of anesthesia to the patient’s spontaneous breathing.Eye-opening time is the time from anesthesia cessation to when the patient can be called to open their eyes.Extubation time is defined as the time from the cessation of anesthesia to the removal of the patient’s tracheal catheter.Post-extubation agitation score. Ratings will be performed immediately after awakening and 15, 30, and 60 min after awakening: 1 point—restful sleep; 2 points—awake and calm; 3 points—irritability or irritability or crying; 4 points—difficulty to comfort or uncontrollable crying; 5 points—unable to be quiet or confused or delirium.Post-extubation sedation score. Ramsay sedation scale will be administered to the patients immediately after awakening and at 15, 30, and 60 min after awakening: 1 point—awake but anxious and restless; 2 points—cooperation, orientation, quiet; 3 points—drowsiness and response to commands; 4 points—drowsiness, rapid response to tapping eyebrow or loud auditory stimuli; 5 points—lethargy, slow response to tapping eyebrow or loud auditory stimuli; 6 points—drowsiness, no response at all. Scores 2–4 indicate satisfactory sedation and 5 to 6 excessive sedation.

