## Background

Loss of vision during prone surgery is a devastating complication that occurs due to a variety of reasons [1]. Intraoperative prone position can cause mechanical damage or ischemia of visual structures, causing postoperative visual loss or visual field defects [2]. The flash stimulus is transmitted from the retina to the optic nerve, optic chiasm, optic tract, lateral geniculate body, optic radiation, and visual cortex and converted from a light signal to electrical conduction. The evoked potential waveforms and data extracted from the occipital lobe area during surgery are called FVEPs. They reflect the integrity of the visual pathway in real time to guide intraoperative decision-making and prevent visual impairment or deterioration of the same caused by visual pathway damage [3–5]. Previous studies have shown that the amplitude is the main measure for evaluating FVEP, in addition to the latency value. Recently, a study showed that setting the early warning value as the FVEPs’ amplitude decreased by 20% from the baseline can detect new quadrant blindness [6]. FVEPs have become a reliable method for intraoperative protection of visual function in procedures jeopardizing visual pathway integrity or visual function, such as spine surgery in the prone position, neurosurgery of the sellar region, and similar.

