### Sample size calculation

We used PASS 15 to calculate the sample size for this study. According to the pre-experiment results, at 60 min after induction of anesthesia, the amplitudes of the LD group and HD group were 3.43 ± 0.78 μV and 2.37 ± 0.80 μV, respectively. According to the results of other studies, the superiority margin was defined as 20% of the N75-P100 amplitude in the HD group [6]. According to *α* = 0.025 and *β* = 0.2, a sample size of 63 cases can provide a superiority margin of 20% higher amplitude in the LD group than in the HD group. We conservatively set the dropout rate at 10% on the basis of actual 1.7% in our previous study, the sample size should be a total of 70 persons will be enrolled, and 35 patients in each group.

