### Statistical analysis

All data analyses will be performed on both a per-protocol (PP) and intention-to-treat (ITT) basis. The intent-to-treat population will include all subjects randomized to receive HD or LD anesthesia maintenance, and the completed FVEP data will be collected. The per-protocol population will include all subjects in the ITT population not identified as protocol violators (i.e., change in the anesthesia strategy after the trial initiates). These protocol violations will be shown in a listing. Subjects who do not obtain available FVEP data or abandon the study for various reasons will be considered to have failed HD/LD and will be excluded from any form of analysis. For the missing data, the last observation and the worst-case imputation scenarios will be used as the main interpolation method.

The statistical analysis will be performed by an independent statistician using SPSS V.25.0 (Somers, NY, USA). Histograms and the Shapiro‒Wilk test will be used to assess the normality of the data distribution. For the statistical description, the continuous variables will be presented as the mean (standard deviation, SD) for normally distributed data or median (interquartile range, IQR) for skewed distributions. Categorical variables will be reported as counts and percentages, and the relative risk with its 95% confidence interval (CI) will be calculated. The absolute standard deviation (ASD) will be determined to identify any imbalance in baseline characteristics.

The primary outcome (N75-P100 amplitude of FVEPs recorded 1 h after induction) will be analyzed using a superiority test. According to the results of other studies, the superiority margin was defined as 20% of the N75-P100 amplitude in the HD group [6].For secondary outcomes, *χ*^2^ tests or Fisher’s exact tests will be performed for categorical variables including N75-P100 amplitude decline rate, P100-N145 amplitude decline rate, rate of prolongation of P100 latency, success rate of FVEP monitoring, FVEP stacking satisfaction, adverse events related to FVEP monitoring, and recovery quality. Anaesthetic and vasoactive drug agent consumption will be analyzed using independent samples *t*-tests for normally distributed variables and Wilcoxon sum tests for variables with skewed distributions. The study will terminate after all the data for the last patient are collected.

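### Percentage change from the TIVA value is an inefficient way to build the three secondary FVEP change endpoints; a baseline-adjusted comparison of the 60-min values would do better

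*Protocol article*

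**What the plan says.** Study endpoints lists three secondary FVEP change measures: the decline rates of the N75-P100 and P100-N145 amplitudes, and the rate of prolongation of P100 latency. Each is a patient's change between two time points divided by that patient's first value and multiplied by 100. The first of them reads "N75-P100 amplitude decline rate compared to baseline measured under TIVA, calculated by the formula", and the denominator is fixed: "N75-P100 (TIVA) will be measured 30 min after anesthesia induction under TIVA in both groups". The second value is taken at 60 min under the allocated regimen.

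Intervention says that each quantity is measured "3 times and record the average of the measurements". For the primary amplitude, Study endpoints also averages over leads and eyes ("the mean N75-P100 amplitude on O1, O2, and Oz leads in both eyes").

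Statistical analysis says that "continuous variables will be presented as the mean (standard deviation, SD) for normally distributed data or median (interquartile range, IQR) for skewed distributions". The same section nevertheless names the three change measures among the categorical variables for chi-square or Fisher tests, and gives no cut-off.

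Background cites a study in which a warning value set at "amplitude decreased by 20% from the baseline can detect new quadrant blindness". Sample size calculation and Statistical analysis use 20% in another way, as the superiority margin for the primary amplitude.

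**The concern.** Patients are randomised only to LD or HD, so these ratios are the trial's only measures of how far each regimen departs from TIVA. For P100-N145 amplitude and P100 latency they are the only endpoints defined. Two properties of the construction matter.

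- **Efficiency.** Dividing by the baseline imposes a fixed form of adjustment instead of estimating it. When the baseline-to-60-min correlation is moderate, the division carries baseline variation into the endpoint: a patient with a chance-low TIVA value tends to show a small or negative decline. Power is lost compared with a model that uses the TIVA value as a covariate.
- **What the mean estimates.** The average of 60-min/TIVA ratios is in general not the ratio of the averages. If the first exceeds the second, the reported mean decline is smaller than the fall in mean amplitude. The mean-or-median rule then lets the observed distribution decide which quantity is reported.

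At stake is the precision and reading of three secondary endpoints, not the primary result.

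**Working it through.** **Figures in the plan.** The documents give no mean, SD or expected value for any decline rate or for the TIVA baseline, so there is no figure of the plan's own to reproduce on this point. The only amplitude data are the pilot values at 60 min: "the amplitudes of the LD group and HD group were 3.43 ± 0.78 μV and 2.37 ± 0.80 μV, respectively". The trial size used below is the planned 63 before dropout (63/0.9 = 70).

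**Inputs.**
- LD CV = 0.78/3.43 = 0.227; HD CV = 0.80/2.37 = 0.338.
- Assumed, because not in the documents: the baseline CV, the correlation ρ between baseline and 60 min (range 0.5 to 0.8), and the shape of the distribution.

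**Mean of ratios, log-normal model.** With X the TIVA value, Y the 60-min value and s² = ln(1 + CV²), the mean of Y/X equals the ratio of means multiplied by k = exp(s_X² − ρ·s_X·s_Y). With equal CVs, k = exp(s²(1 − ρ)).

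- CV 0.227: s² = 0.0504; k = exp(0.0252) = 1.026 at ρ = 0.5 and exp(0.0101) = 1.010 at ρ = 0.8.
- CV 0.338: s² = 0.1079; k = exp(0.0540) = 1.055 at ρ = 0.5 and exp(0.0216) = 1.022 at ρ = 0.8.

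Mean reported decline = 1 − (1 − true fall) × k:

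| True fall in mean amplitude | CV 0.227, ρ 0.5 / 0.8 | CV 0.338, ρ 0.5 / 0.8 |
|---|---|---|
| 15% | 12.8% / 14.1% | 10.3% / 13.2% |
| 22% | 20.0% / 21.2% | 17.7% / 20.3% |
| 25% | 23.1% / 24.2% | 20.8% / 23.4% |
| 30% | 28.2% / 29.3% | 26.1% / 28.5% |

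The largest understatement is 15 − 10.3 = 4.7 points.

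**The sign is not fixed.** With baseline CV 0.227, 60-min CV 0.338 and ρ = 0.8, k = exp(0.0504 − 0.8 × √(0.0504 × 0.1079)) = exp(−0.0086) = 0.991. A true 25% fall then averages 1 − 0.75 × 0.991 = 25.6%. With normal data, SD 0.80 at both times and a 60-min mean of 2.37, a true 22% fall averages 19.3% at ρ = 0.5 and 22.1% at ρ = 0.8.

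**Median.** With equal CVs in the log-normal model, the median ratio returns the true fall at every ρ. With unequal CVs it describes the typical patient's ratio (27.1% where the fall in means is 25%, at CVs 0.227 and 0.338), which is a different target and not an error.

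**Between-arm contrast.** With equal CVs in both arms, the same k multiplies both arms' ratios. At CV 0.338, a 15-point difference becomes 15 × 1.055 = 15.8 points at ρ = 0.5 and 15 × 1.022 = 15.3 at ρ = 0.8. With no true difference, simulated type I error stays at about 5% for both methods, so the comparison is valid.

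**Power.** Simulated two-sided 5% tests, 32 and 31 patients, true declines 15% and 30%; Welch t-test on percentage change against ANCOVA of the 60-min value on arm and TIVA value:

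| Model | ρ | Percentage change | Log ANCOVA | Raw ANCOVA |
|---|---|---|---|---|
| Log-normal, CV 0.338 | 0.5 | about 61% | about 75% | about 72% |
| Log-normal, CV 0.338 | 0.7 | about 84% | about 89% | about 87% |
| Normal, SD 0.80 | 0.5 | about 73% | about 76% | about 81% |
| Normal, SD 0.80 | 0.7 | about 92% | about 90% | about 93% |

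Adjusting for baseline helps in each setting when the scale suits the data. In the normal model, log ANCOVA beats percentage change only at ρ of about 0.6 or lower.

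**The case against.** The strongest reply is that a mean per-patient percentage decline is a legitimate quantity, close to how clinicians express a warning, and that the choice of scale for a secondary endpoint is often left to an analysis plan. Part of this stands: the between-arm comparison is valid and the measure is not wrong in itself. However, the article does fix the construction with explicit formulas, so this is a stated choice that can be improved.

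Several other objections also stand.
- The arithmetic mean is not fixed as the summary. The median is allowed, and the three measures are listed as categorical.
- No noise figure is given for the TIVA value, and averaging repeated measurements reduces noise, though it does not remove real variation between patients or over time.
- The bias depends on quantities that the documents do not give. The nearly equal pilot SDs (0.78 and 0.80) at different means hint at a constant SD, under which the bias shrinks and can reverse.
- The power comparison uses a t-test that the article does not assign to these endpoints, and the largest gain arises in a model that suits the log scale.
- No SD is given for P100-N145 amplitude or P100 latency, so none of the figures above is calculated for them.

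A reader might also infer that an arm whose amplitude falls by more than the cited 20% will be reported as falling by less. The documents do not support that. The 20% in Background is a warning value for one patient against that patient's own baseline, where no averaging bias arises, and no planned rule sets a group mean against it. Even under the assumptions above, such a crossing occurs only for true falls a little over 20% at ρ 0.5 to 0.8, and not at all where the bias vanishes or reverses.

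**Conclusion.** The point holds as a minor improvement to secondary endpoints. Percentage change from a single TIVA time point uses the baseline inefficiently, and its arithmetic mean can understate the fall in mean amplitude by roughly 0 to 5 points at correlations of 0.5 to 0.8. The baseline CV, the correlation and the distribution are all assumed; the documents settle neither the size nor the sign of the bias. The efficiency gain is the firmer argument: about 61% to 75% power at ρ = 0.5 in the log-normal model, shrinking as the correlation rises and depending on the scale chosen. It does not follow that desflurane will be made to look safer, or that the comparison of LD with HD is biased towards a false positive. The primary endpoint, an absolute amplitude at 60 min, is unaffected.

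**What to change.** In Study endpoints and Statistical analysis, treat N75-P100 amplitude change, P100-N145 amplitude change and P100 latency change as continuous. For each, compare the 60-min value between arms by ANCOVA with arm and the 30-min TIVA value as terms. Prespecify the scale. The log scale (log 60-min value on arm and log TIVA value) is a reasonable choice because it gives a geometric mean ratio that reads as a percentage. Report the LD/HD ratio with its 95% CI, and each arm's geometric mean ratio to TIVA as a within-arm description. Keep the individual percentage changes as descriptive data.

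The cost is analysis wording only: the same measurements are used, no patients are added, and results can still be read as percentages. The one downside is dependence on the chosen scale: if amplitudes are close to normal with constant SD, raw-scale ANCOVA would be more efficient than the log version, so the scale should be fixed before the data are examined by arm.
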